15. Aged 55 years or older;
16. Low blood pressure or history of significant dizziness
17. trial design

Participants will be randomized to receive either *R. rosea* or identical placebo to be taken daily over a six week period (Error: Reference source not found).

Randomize

Population

Eligible

Sample

Placebo

No intervention

*Rhodiola rosea*

Enrolment (4 weeks before trial start)

Baseline (start of clinical rotation)

Week 10

(End of clinical rotation)

Week 3

Week6

**Figure 1:** Trial Design Schematic

- - 1. RECRUITMENT, informed consent and enrollment

In collaboration with the Faculty of Nursing, students enrolled in NURS 495 will receive notification of the study by way of an introductory email with an information sheet attached in December 2010. The ~~study~~ **project** coordinator will make in-class visits during the first two weeks of January 2011 to answer any study-related questions and to schedule an appointment for eligibility assessment with the study nurse for interested persons. During the eligibility assessment subjects will be given the information sheet to read over and have study procedures explained to them in detail by the study nurse***.*** Subjects will sign the consent form prior to being screened against the selection criteria***.*** All eligible subjects will then be enrolled, randomized and receive their assigned medication from the study nurse during the first visit. However, female participants will need to undergo a blood pregnancy test to ensure they are not pregnant for which they will be given a lab requisition by the study nurse. A total of 2 mL of blood will be withdrawn for this test***.*** When lab results are received by the principal investigator, those with tests confirming they are not pregnant will contacted by the study nurse to confirm their enrolment. Females whose tests indicate positive for pregnancy will be called by the study physician ([name]) and asked to return the study medication they received to the study nurse. The participant will then be contacted by the study nurse to schedule a drop-off date and time. During the enrolment visit, the study nurse will also review all outcome measurement tools and walk subjects through a pilot of the tools to be used during the study.

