All participants will begin the study on the same, fixed date when their shift work begins (date to be finalized in January 2011). Since data collection will be electronic via the internet, study participants are expected to have internet access. If participants know they will not have internet access or reliable access, arrangements will be made to give them either paper or offline electronic data collection forms (as well as a pre-paid envelope to send the forms back in).

- - 1. STUDY VISITS, phone calls and email reminders

In addition to the initial study visit and phone calls described in section 5.1.1., the project coordinatorwill phone each subject within 3 days of the study start to review study procedures and outcome assessment documentation procedures. At this time, the project coordinator will inquire about effectiveness of the blind and about participant beliefs about medication effectiveness. The next call from the project coordinator to participants will occur during the 2nd week of the study (days 14 to 20) inquire about adverse effects and to remind them of completion of the outcome assessment forms to be filled out~~.~~ The project coordinator will call study participants during the 5th week of the study (days 35 to 41) to remind them of the forms to be filled out, inquire about adverse effects and schedule a follow-up visit for when they are finished their clinical rotation at the end of 10 weeks. Throughout the study, subjects will also receive daily email reminders containing a link to the online data collection forms for that day. At the 10-week mark (day 70), participants will be sent an email reminder to complete all outcomes assessment forms for the final time. At this time, they will again be queried about their thoughts on effectiveness of the study medication. They will then return any unused study medication to the study nurse during their final scheduled visit.

1. trial INTERVENTIONS

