**The following interventions will be supplied:**

1. ***Rhodiola rosea* extract standardized to2.8% rosavins (**29.0 % microcrystalline cellulose, 0.5% Silicon dioxide
2. **Placebo (**95% microcrystalline cellulose, 0.5% Silicon dioxide)

**Both interventions will be encapsulated in gelatine capsules, which are an animal-based product, and will look identical. Medications will be packaged in identical bottles labelled according to the participants’ randomization code.**

Development of the both interventions will be undertaken by [name] [name], a pharmacist and assistant professor in the Faculty of Pharmacy and Pharmaceutical Sciences at the University of Alberta. [name], will store all trial medications (*R. rosea* and placebo) in a secured storage facility until recruitment. Study medication will then be given to the study nurse for dispensing at time of enrolment; medication will be stored under lock and key accessible only by the study nurse until time of dispensing.

- 1. Treatment regimen

The trial will begin on the day that subjects start their clinical rotations and end 6 weeks later. Subjects will be instructed to take two to four capsules of the trial medication per 24 hour period (see section 6.2). All outcomes will be measured at baseline (Day 0) and at the end of the trial period (week 6). The project coordinator will phone participants on the day(s) leading up to their baseline assessment to remind them to complete their questionnaires and ensure they are comfortable with the study procedures. The primary outcome and two secondary outcomes will be measured again at the end of each week; all other outcomes will be measured daily (see section 7). Subjects will be prompted to report adverse events daily during the trial period and at the end of their clinical rotation four weeks after completion of the trial. During the trial period, the study nurse will phone participants in week 2 and week 5to remind them to complete their questionnaires and to inquire about adverse events (see section 7.1.2).

- 1. DOSE AND DURATION

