**The code for a patient will only be opened in an emergency, when it is necessary for a patient’s treatment to be disclosed. If a code is broken the investigator will inform the Study Director/Monitor and document the details of the reason in the patient’s case report forms.**

- 1. ALLOCATION CONCEALMENT

Participants will receive a sealed, serially-numbered opaque bottle containing the study medication or placebo depending on their randomised group assignment. They will be provided a six-week supply of their assigned study medication.

- 1. BLINDING

**The placebo capsule will have the same appearance, volume, weight, odour and taste as the *R.rosea* product so that neither the participant nor trial personnel know who is receiving which medication. The effectiveness of the blind will be assessed at the beginning of the study after a single dose via the MYMOP on Day 1. Participants will be asked to guess which medication they think they were allocated to.**

- 1. **CO-INTERVENTION AND CONTAMINATION**

**Since stimulant medications have been identified as potentially hazardous to combine with *R.rosea*, subjects being recruited will be considered ineligible for the trial if they are using such medication. As part of their daily questionnaires, participants will be asked to record any medication used (prescription, over-the-counter, or natural health product) and quantity of caffeine and alcohol consumption in the past 24 hours to ensure that important co-variables can be considered in the final analysis. These questions will be administered as part of the daily MYMOP assessment.**

**From the start of the treatment, participants will be advised not to take any rhodiolaor ginseng preparations for the duration of the trial so that only the *R. rosea* treatment will influence trial outcomes. Furthermore, they will be informed that there is a 50% that they may be receiving *R.rosea*, the dose of which is being in this trial is the highest that has been supported by evidence of safety, and cautioned that they would therefore not want to “double-dose” themselves.**

- 1. **ACCOUNTABILITY OF TRIAL MEDICATION**

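### The one planned pregnancy test has no set draw date, capsules are handed out before its result, and no described contact before the first dose asks about pregnancy again

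*Protocol*

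**What the plan says.** Protocol section 4.2 excludes pregnant and breastfeeding women, requires the blood test as confirmation, and gives the absence of safety data as the reason; section 1.2.3 says the same about safety data. Section 4.2 also excludes women of child-bearing potential who do not use birth control during the trial.

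Section 5.1.1 sets the order of events: "All eligible subjects will then be enrolled, randomized and receive their assigned medication from the study nurse during the first visit". It then adds that "female participants will need to undergo a blood pregnancy test to ensure they are not pregnant for which they will be given a lab requisition". After the laboratory reports, "those with tests confirming they are not pregnant will contacted by the study nurse to confirm their enrolment"; a woman with a positive result is called and asked to bring her medication back. Section 6.4 describes the amount handed over: "They will be provided a six-week supply of their assigned study medication".

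The only stated interval between enrolment and start is the Figure 1 label, "Enrolment (4 weeks before trial start". Section 5.1.1 fixes the start for everyone together: "All participants will begin the study on the same, fixed date when their shift work begins (date to be finalized in January 2011".

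Two contacts are described around Day 0. In section 5.1.2 the coordinator will "phone each subject within 3 days of the study start to review study procedures and outcome assessment documentation procedures", and asks then about the blind and about beliefs in the medication. Section 6.1 adds an earlier one: "The project coordinator will phone participants on the day(s) leading up to their baseline assessment to remind them to complete their questionnaires". It also covers whether participants are comfortable with the procedures.

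**The concern.** The protocol makes a blood test the means of verifying a safety exclusion, but does not connect that test to the first dose. The requisition belongs to the enrolment process, while the first dose belongs to the common start date. A woman who goes to the laboratory promptly, and conceives despite contraception before Day 0, could begin *R. rosea* or placebo on a result that no longer describes her. She already holds the whole supply, so no later dispensing visit can act as a checkpoint.

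The same arrangement leaves a second, smaller opening. Enrolment is confirmed only after a negative result, but the text does not say that capsules must stay unopened until that confirmation. What is at stake is exposure of a pregnancy to a product for which the protocol says no pregnancy safety information exists.

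**Working it through.** **Order of events (sections 5.1.1, 6.1, 6.4 and Figure 1)**

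1. First visit: consent, screening, randomization and dispensing of a six-week supply. The requisition is given in this enrolment process.
2. Blood draw: date not stated.
3. Result received, then the nurse's contact to confirm enrolment. This is triggered by the result, not by Day 0. It passes the result on and does not update it.
4. Coordinator's call on the day(s) before baseline: pregnancy not mentioned.
5. Day 0: common start date.
6. Coordinator's call within 3 days of the start: pregnancy not mentioned. Because it asks about the blind, which section 6.5 assesses after a single dose, it may come after dosing has begun.

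That capsules leave the clinic before the result is confirmed by the instruction to women who test positive: they are asked to return medication they already have.

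**Age of the result**

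Inputs: enrolment-to-start interval of 4 weeks (Figure 1, nominal); dosing for 6 weeks (section 6.1).

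- Age at first dose = days from draw to Day 0. Drawn at enrolment: 4 × 7 = 28 days. Drawn just before Day 0: about 0 days. Range under the nominal schedule: 0 to about 28 days.
- Dosing period: 6 × 7 = 42 days. Longest time from the only test to the end of dosing: 28 + 42 = 70 days. The last 42 of these are untested wherever the draw falls before Day 0.

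The 4 weeks cannot be reproduced from the text. Class visits fall in the first two weeks of January 2011, appointments follow from them, and the start date was still to be finalized.

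**What moving the draw would do**

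Take a draw on Day -10, -7 or -5 (illustrative), so that the result is 10, 7 or 5 days old at first dose. Reduction = interval − age at first dose, compared with a draw at enrolment:

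| Enrolment-to-start interval | Day -10 | Day -7 | Day -5 |
| --- | --- | --- | --- |
| 28 days (Figure 1) | 18 | 21 | 23 |
| 21 days (assumed) | 11 | 14 | 16 |
| 14 days (assumed) | 4 | 7 | 9 |

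There is no gain if draws already fall in that window. Time left before Day 0 = days from draw to start − turnaround. With an assumed turnaround of 1 to 3 days this is 7–9, 4–6 and 2–4 days respectively.

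The documents give no basis for estimating a number of pregnancies, so none is estimated.

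**The case against.** The strongest reply is that nothing here is stated wrongly. Only the requisition is issued at enrolment; the draw is left open, so a result 0 days old fits the text as well as one 28 days old. The 28 days rest on one label in a figure that the narrative does not repeat. A reader might infer that the protocol fixes the test itself at four weeks before dosing. The documents do not support that reading, and the interval is a ceiling only.

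There are also safeguards. The birth-control criterion lowers the risk. Section 7.1.3 withdraws anyone who meets an exclusion during the trial, which would include a woman who conceived before Day 0 and is therefore pregnant from the first dosing day. Section 7.1.2 provides daily adverse-event queries and regular nurse calls through which a pregnancy could come to light. The call descriptions state purposes and are not scripts, and the consent pages, which may tell participants to report a pregnancy, are not available and are not judged here.

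Most of this is fair and limits the point. It does not remove it. The birth-control criterion does not verify status, the withdrawal rule acts only once a pregnancy is known, and the daily queries run during the trial period. None is a check before the first capsule.

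A reader might also conclude that the draw has to be moved close to Day 0. That does not follow. An early draw identifies women already pregnant at enrolment and leaves time to recover their capsules. A late draw makes them hold the capsules longer without a result and shortens the time to retrieve them.

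**Conclusion.** The point holds as a minor, optional improvement to participant safety. Followed as written, the protocol allows a first dose to rest on a result anywhere from 0 to about 28 days old, with the capsules already in the participant's hands and no described step that asks about pregnancy again before dosing. The upper figure assumes that the Figure 1 interval applies and that blood is drawn at the enrolment visit; a shorter true interval lowers it day for day.

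Confidence is medium, because both the draw date and the true interval are unknown. The point concerns only eligibility timing and exposure and has no effect on sample size, alpha or the primary comparison.

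**What to change.** Two additions to the wording:

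- **Section 5.1.1:** state that no woman takes a first capsule until a negative blood result is on file and the study nurse has confirmed her enrolment.
- **Section 6.1:** add one pregnancy-status question to the coordinator's call already planned before baseline, and hold dosing if the answer raises doubt. A repeat test would be needed only for those women.

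This adds no planned visits, calls or routine tests. The downside is that a woman with a late result or a doubtful answer may start after the common date or not start at all.

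Moving the draw to about Day -7 is a further option for the qualified investigator to weigh. It gives a fresher result but less time to recover capsules, and if it is chosen the hold on the first capsule matters more.

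The two additions put a check before the first dose but do not address conception during the 42 dosing days.

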All primary analyses will apply the intention to treat principles. All statistical tests are two-sided and tests will be evaluated against 0.05 level of significance. Estimates and corresponding 95% confidence intervals will be reported. The RAND-36 vitality subscore will be used as the primary indicator of the efficacy of *R.rosea*. To test the main hypothesis of the effects of *R.rosea* in reducing fatigue of nurses involved in shift work, the mean change from baseline to six weeks of the vitality subscore using RAND-36 will be compared between the *R.rosea* and placebo groups. This 2-sample t-test will be supplemented by additional analyses using rate of change outcome measure. Linear mixed model will be employed to test changes in the intercept and slopes of the treatment groups. This type of modelling accounts for the variability and correlatedness of the observations on the same participant. Despite the tendency of participants to miss testing occasions, the mixed model analyses can still evaluate any trajectories of change. Missing data will be checked for randomness and correlation with adverse events will be explored. Since RAND-36 vitality subscore is not validated for use in this specific population, correlatedness between it and a visual analogue scale for fatigue (VAS-F) will be tested. In addition, correlatedness between ACI, will be tested against the primary outcomes in order to establish further evidence of validity. RAND-36 physical and mental component scores will be analysed by testing their mean change from baseline to day 42 between treatment groups, as a secondary outcome. Mixed model analyses will be applied for testing change for VAS-F, RAND-36, ACI and MYMOP. Side by side graphs of the rates of change between treatment groups will be plotted at the exploratory and final stages of analysis. Examination of the effect of the covariates - concurrent medication, dose-related change, sleep, alcohol use and impact of specific rotation (rotating vs permanent shift-work), age and marital status will be analyzed using linear mixed regression models as secondary outcomes. SAS 9.1 (Cary, N.C.) will be used for data management and statistical models. SPSS (Michigan) or Splus/ R will be used for supplemental graphs.

Adverse events will be monitored daily. Rates of adverse events will be compared between the two groups using the chi squared test at baseline, day 21 and day 42 measurements.

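### The only baseline is a self-completed form scheduled about four weeks after randomisation, so a randomised participant who misses it falls out of the primary test

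*Protocol*

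**What the plan says.** Section 5.1.1 places consent, screening, randomisation and dispensing at one visit: "All eligible subjects will then be enrolled, randomized and receive their assigned medication from the study nurse during the first visit". Figure 1 labels that step "Enrolment (4 weeks before trial start" and labels the later measurement "Baseline (start of clinical rotation". Section 6.1 fixes baseline as Day 0, and neither 6.1 nor 7.1.1 schedules an earlier outcome measurement. Section 9 makes every questionnaire self-reported through the online system.

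At the enrolment visit the nurse will also "walk subjects through a pilot of the tools to be used during the study". The protocol does not say whether this comes before or after randomisation, whether it yields scores, or what becomes of them.

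Two sections describe a call around the start. In 6.1: "The project coordinator will phone participants on the day(s) leading up to their baseline assessment". In 5.1.2 the coordinator will "phone each subject within 3 days of the study start", and that call also asks about the effectiveness of the blind.

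Exclusion criterion 11 bars concurrent use of other rhodiola or ginseng products and is applied at screening. Section 6.6 dates the advice differently: "From the start of the treatment, participants will be advised not to take any rhodiolaor ginseng preparations".

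Section 8.2 compares mean change in vitality from baseline to six weeks by t-test under intention to treat. It introduces the supplementary mixed model with the words "Despite the tendency of participants to miss testing occasions".

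**The concern.** A change score needs both ends. Here the first end is a single unsupervised form due weeks after the participant has been randomised and has taken the bottle home. If it is missed, the person cannot enter the primary t-test even with complete data from Day 7 to Day 42. That sits badly with the intention-to-treat statement, and the protocol itself expects missed occasions.

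Section 5.1.1 also creates a route out before Day 0. Women are randomised and given product before the pregnancy result is known, and those who test positive are asked to return it.

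The order of events on Day 0 is a further gap. The trial period starts that day (6.1) and capsules are taken at the start of the wakeful period (6.2), but nothing says the baseline form comes first. A form completed after a dose is not a true baseline. At stake are the completeness of the primary comparison and certainty about what its baseline measures.

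**Working it through.** **Sequence, set side by side**

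1. Enrolment visit, about week −4 by the Figure 1 label: consent, screening, randomisation, bottle handed over, tools walked through (5.1.1).
2. Interval: no outcome form is scheduled. Capsule counts and co-medication come from the daily MYMOP (6.2, 6.6), for which no use before the study start is described.
3. Day 0: baseline form due and trial period begins (6.1).
4. Day 1: guess at allocation, after a single dose (6.5).
5. Start call: before baseline in 6.1, within three days of the start in 5.1.2. A question about the blind makes most sense after a dose, which is too late to prompt the Day 0 form. The two passages probably describe one call. Section 7.1.2 has the third call schedule the final visit, and 5.1.2 gives that task to the week-5 call, which leaves one call before week 2.

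**The protocol's sample size**

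Inputs from 8.1: 64 participants (read as the total, 32 per arm), difference 6.5, two-sided alpha 0.05, power 90%. No SD is given, so 64 cannot be reproduced independently. It can only be inverted:

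- Normal approximation: SD = 6.5 / [(1.960 + 1.2816) × √(2/32)] = 6.5 / (3.2415 × 0.25) = 8.0.
- Exact t-test: SD = 7.9, a standardised difference of 0.823.

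If 64 were per arm, the implied SD would be about 11.3.

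The protocol inflates to 90. A 40% loss from 90 leaves 90 × 0.6 = 54. (90 matches 64 × 1.4 = 89.6, whereas 64 / 0.6 gives 107. That is a separate matter, but it is why both 64 and 54 are shown.)

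**Effect of a missing Day 0 form**

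Let m be the assumed share of otherwise evaluable participants without a Day 0 form. The number analysed is N(1 − m). Power, normal approximation: Φ(3.2415 × √[N(1 − m)/64] − 1.960).

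- N = 64, m = 10%: 57.6 remain; 3.2415 × √0.900 − 1.960 = 1.115; power 0.868 (exact t 0.866).
- N = 54, m = 0: 3.2415 × √0.844 − 1.960 = 1.018; power 0.846 (exact t 0.843).
- N = 54, m = 10%: 48.6 remain; 3.2415 × √0.759 − 1.960 = 0.865; power 0.806 (exact t 0.802).

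Range by exact t-test, all rates of m assumed:

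| m | Analysed from 64 | Power | Analysed from 54 | Power |
|---|---|---|---|---|
| 0 | 64 | 90% | 54 | 84% |
| 5% | 60.8 | 88% | 51.3 | 82% |
| 10% | 57.6 | 87% | 48.6 | 80% |
| 20% | 51.2 | 82% | 43.2 | 75% |

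In the approximation, power depends only on the ratio of the number analysed to the number planned, so reading 64 as per arm barely changes these figures.

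**The case against.** The baseline is far from unprotected. There is one fixed start date, a call planned before baseline in 6.1, daily email links, paper or offline forms for those without internet, training in the tools at enrolment, and a matched blinded placebo. A blinded baseline taken after randomisation but before any dose is not biased in itself, and the start of shift work is a sensible moment to measure. The supplementary mixed model can use later scores from someone without Day 0, and covariate choice and missing-data handling often belong in an SAP, which is not shown. The 40% allowance is not limited to losses after Day 0, so early leavers may already be counted in it.

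Most of this stands and limits the size of the point. It does not remove it. The protocol itself fixes the primary test as a change score and fixes the schedule. An SAP cannot later supply a pre-randomisation score that was never collected.

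A reader might go further in four ways that the document does not support:

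- That the enrolment scores are discarded. The protocol is silent, and a guided demonstration need not produce a score. It only makes no provision to keep one as a baseline.
- That the baseline is uncontrolled. The safeguards above show otherwise.
- That capsules will be taken in the weeks before Day 0 and dilute the effect. Nothing suggests this, and 6.5 places the first dose at about the trial start, so no figure is put on it.
- That criterion 11 and section 6.6 contradict each other. One applies at screening and the other from the start of treatment. They leave the interval uncovered, which is a gap rather than a conflict.

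**Conclusion.** The point holds as an inexpensive improvement that should be made, not as a fatal flaw. The primary analysis depends on a post-randomisation form that can be missed, no rule orders that form before the first capsule, and the call meant to prompt it has two timings.

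For 10% missing Day 0 forms the cost is about 3 to 4 percentage points of power (90% to 87%, or 84% to 80%). For 5% to 20% it runs from about 2 to 9 points. This rests on assumed missingness, on an SD inferred from the stated sample size, and on missingness unrelated to treatment. If it differed by arm, bias would be possible too. The four-week interval rests on one figure label. The start date was still to be finalised and visits were scheduled individually, so it will vary between participants.

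**What to change.** 1. In 5.1.1, have the RAND-36, VAS-F and ACI completed and stored at the enrolment visit before randomisation, and add that time point to the schedule in section 7. In 8.2, analyse the week-6 vitality score adjusted for baseline, using the enrolment score alongside Day 0, and alone when Day 0 is missing.
2. State that the Day 0 form is completed before the first capsule. Reconcile 5.1.2 and 6.1 so that one call precedes Day 0 and records any study capsules or other rhodiola or ginseng taken since enrolment.
3. Reconcile criterion 11 and section 6.6 so that the protocol says what applies between enrolment and Day 0.

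The cost is some form time at a visit where the nurse already goes through the tools, two questions on a planned call, and a short change to 8.2. The enrolment score may be about four weeks older than Day 0 and is taken before shift work begins, so it should supplement Day 0, not replace it. It gives every randomised participant a baseline value. It does not supply a missing week-6 value.
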